#### Statistical Models for Objective H1B

We will use a logistic regression with OCD severity categories moderate and severe-extreme as the outcomes. We denote the severity *s* = 0, 1. We will fit the following logistic regression model to the scores:

logit(si) = θ + b1

i + b2

i + εi (2)

where *ε_i_* ∼ *N* (0, *σ*_2_*_j_*) and v*_j_* is the *j*th latent vocal feature adjusted for age and gender and averaged over the 10 repetitions for each youth, as described in the following.

This analysis aims to test the effects from vocal features on the severity scores through the null hypotheses that *b*_1_ = 0 and *b*_2_ = 0, which we will test at a 1.25% level of significance.

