## Methods

### Participants and Setting

We will include audio recordings from a total of 64 youths aged 8 to 17 years (47 with OCD and 17 healthy controls). The audio recordings of diagnostic interviews stem from a large randomized clinical trial and case-control study of OCD, called TECTO [17]—TECTO runs at a public hospital in Denmark.

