#### OCD Severity

Trained mental health professionals assessed the clinical severity of OCD using the Children’s Yale-Brown Obsessive Compulsive Scale (CY-BOCS) [19]. The CY-BOCS interview begins with a checklist of obsessions and compulsions to establish which symptoms have been present over the past week. On a scale from 0 to 4, clinicians rate 5 items on the severity of obsessions and 5 items on the severity of compulsions. Severity is rated on 5 dimensions: level of distress caused by the symptoms, functional interference, time consumed by symptoms, and resistance to and degree of control over symptoms. A total severity score is calculated by summing all 10 items on a scale from 0 to 40. Although CY-BOCS scores are continuous, a previous study of 815 youth between the ages of 4 and 18 years found the following cutoff scores to be consistent with global clinical severity ratings: 0-7, subclinical; 8-15, mild; 16-24, moderate; and 25-40, moderate-severe to severe [20]. A CY-BOCS score of ≥16 was required to be included in the study.

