### Statistical Analysis Plan

The planned study has two main objectives:

Test the usefulness of a previously learned latent model, composed of 2 dimensions representing a compressed vocal feature space guided by activation labels [16], as a marker for OCD diagnosis and severity.Learn a new latent model, which we will propose as an improved candidate indicator of OCD severity.

Our first objective will be achieved through 2 statistical analyses, with the following hypotheses:

Objective 1 (H1): an ANOVA will be conducted to test the first research hypothesis (objective H1A) that there is an effect of diagnosis (OCD vs no psychiatric diagnosis) on the vocal feature latent model. With logistic regression (H1B), we will test hypothesis H1, which states that there is an effect of the vocal feature latent model on OCD severity classifications in moderate to extreme OCD cases, with the vocal feature latent model corrected for age and gender. This analysis will only include patients with OCD, and we will examine the classification accuracy of this model.Objective 2 (H2): the second objective will be achieved through data labeling and machine learning modeling. Here, outcomes will include diagnostic status (OCD vs no psychiatric diagnosis) and OCD severity (CY-BOCS severity scores). We will validate the modeling using a leave-two-individuals-out cross-validation and prediction accuracies. Subsequently, we will assess the obtained results using an independent test. We will extract data from 10 of the youths’ audio samples post machine learning modeling for this purpose.

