#### Adjusting for Confounding and Calculating Average Features

We expect age and gender to have an influence on the vocal features and would like to remove these confounding effects from the signals. We will exclude effects from age, gender, and age and gender interactions from the vocal features through a linear regression, as follows.

First, we will find the confounding effects using a linear regression model, which estimates age and gender contributions to vocal features as follows:

where, for the *i*th observations and *j*th vocal feature, *j* = 1, 2. The vocal features adjusted for age and gender are then as follows: 

Finally, we will use the average vocal features over the 10 repetitions for the *k*th youth to obtain 

*_jk_* = Σ*iεyouth_k_ v_ji_* / 10.

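### H1B tests severity on a two-class version of CY-BOCS although the full score is held, which costs power by an amount that depends on unstated assumptions

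*Protocol article*

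**What the plan says.** Under Statistical Models for Objective H1B, the protocol article sets the outcome: "We will use a logistic regression with OCD severity categories moderate and severe-extreme as the outcomes". The two slopes, b1 and b2, are each tested at 1.25%. The same section, and the section on multiple testing, describe these as effects on severity scores.

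The OCD Severity section says of the measure: "Although CY-BOCS scores are continuous". It gives the bands "16-24, moderate; and 25-40, moderate-severe to severe" and the entry rule "A CY-BOCS score of ≥16 was required to be included in the study". The H1B section gives no numerical cut, and its upper label (severe-extreme) differs from that of the band. A cut between 24 and 25 is therefore an inference, though it is the only band boundary within the patients' range of 16 to 40.

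On covariates the article says: "We will exclude effects from age, gender, and age and gender interactions from the vocal features through a linear regression". Equation (2) then holds an intercept, two vocal-feature terms and an error, with no age or gender term. H1A, by contrast, enters age, gender and their interaction directly.

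The Statistical Analysis Plan section frames H1B as an effect on severity classifications and adds: "This analysis will only include patients with OCD, and we will examine the classification accuracy of this model". It also names CY-BOCS severity scores as an outcome for Objective 2.

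**The concern.** Cutting the score treats 16 and 24 as the same and 24 and 25 as different. With at most 47 patients and a 1.25% level there is little information to spare, and the Limitations section concedes a raised type II error risk. If the cut removes much of the power, a null H1B result says little about whether the vocal features track severity.

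A second, smaller issue is the covariates. Removing age and gender from the features but not entering them in the severity model leaves any age or gender effect on severity in the unexplained variation.

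**Working it through.** **Level.** Four tests with Bonferroni: 5%/4 = 1.25%, as stated. Taken as two-sided, the normal critical value is z(1 − 0.00625) = 2.498.

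**Inputs from the article.** 47 patients; score range 16-40; two classes; two features averaged over 10 segments; age, gender and age×gender as adjustment variables.

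**Assumed, because the article does not give them.** Partial correlation of one feature with severity 0.2 to 0.5; share severe 30% or 50%; age and gender unrelated to severity; normally distributed severity. The article does not say whether the slopes are tested by Wald or likelihood ratio (LR), so both are shown.

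**Simulated power for one slope.** Linear regression of the score on v1, v2, age, gender and age×gender, against logistic regression of the class on the two residualised features:

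| Correlation | Linear | Logistic, Wald | Logistic, LR |
|---|---|---|---|
| 0.2 | 11% | 3-5% | 6-10% |
| 0.3 | 28% | 9-11% | 15-19% |
| 0.4 | 57% | 19-27% | 31-38% |
| 0.5 | 85% | 41-49% | 56-63% |

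Taken cell by cell, the loss is about 6-8 points (Wald) or 2-5 (LR) at 0.2, and about 32-44 or 21-29 at 0.4-0.5. At 0.3 the table gives 28 − 11 = 17 to 28 − 9 = 19 (Wald) and 28 − 19 = 9 to 28 − 15 = 13 (LR). Subtracting the rounded entries at 0.4-0.5 gives 30-44 and 19-29; the difference is simulation error and rounding. A repeat with 4,000 simulated data sets per cell agreed with the table to within about three points.

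**Check by formula.** Cutting a normal variable so that a share p is severe multiplies its correlation by φ(z)/√(p(1−p)): 0.399/0.5 = 0.798 at p = 0.5, and 0.348/0.458 = 0.759 at p = 0.3. Power ≈ Φ(√m · atanh(r) − 2.498), where m = 47 − 3 − (number of other terms).
- Linear, r = 0.5, four other terms, m = 40: 6.325 × 0.549 − 2.498 = 0.976, power 84%.
- Two classes, p = 0.5, r = 0.5 × 0.798 = 0.399, one other term, m = 43: 6.557 × 0.422 − 2.498 = 0.27, power 61%.
- Two classes, p = 0.3: 55%.

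The loss is 23 to 29 points at 0.5, close to the LR figures. The Wald test loses more because it is conservative in samples this small.

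**Truncation at 16.** With integer scores limited to 16-40, cut at 24/25, and features residualised on all 64 youths, the result at correlation 0.4 was:
- 56% severe: linear 56.7%, Wald 25.6%, LR 37.1%.
- 34% severe: linear 55.7%, Wald 21.6%, LR 34.1%.

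The picture does not depend on untruncated normal scores.

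**Separating the two causes.** Keep the continuous score and change only the covariate handling, at correlation 0.4:
- Age and gender unrelated to severity: 58.8% with covariates, 58.4% with residualised features only.
- Age and gender related to severity (an assumed effect of 0.4 SD): 59.5% against 49.1%.

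Under the null, with an assumed age-severity correlation of 0.6, the two-stage logistic test rejects about 0.3-0.75% of the time (LR) or about 0.2% (Wald), against a nominal 1.25%. That is conservative, not anti-conservative.

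**The case against.** The binary outcome is a stated choice. The abstract and the Statistical Analysis Plan section speak of severity classifications, classification accuracy is wanted, and Model 1B is to report an ROC curve, sensitivity and specificity. The bands come from a study of 815 youth in which they agreed with global clinical ratings. This stands as a reason to keep the logistic model for classification. It does not require the confirmatory tests of b1 and b2 to use the cut outcome, and the H1B and multiple-testing sections themselves speak of scores.

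The size of the loss is also not a property of the document. A reader might infer that the plan forfeits 25 to over 40 points of power. The article gives neither effect size nor severity split; losses above 40 appear under the stated assumptions only with the Wald test at a correlation near 0.5 and about 30% severe, and at 0.2 the loss is a few points.

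Three further readings are tempting and not supported:
- That residualising biases the test. In a linear model, residualising the features in the same sample gives the same slope as including the covariates. The cost is precision, and only if age or gender relates to severity, on which the article is silent.
- That the first-stage regression is fitted on people other than the 47 patients. Its equations are missing from the text available for review, so the sample cannot be established.
- That the authors call type II error their main limitation. The Limitations section lists the small sample first among several challenges without ranking it.

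**Conclusion.** The point holds in limited form. H1B's confirmatory test uses a two-class version of a score already held in full, and under the assumptions examined it has less power than linear regression with covariates in every case. With 47 patients and a two-sided 1.25% level, the difference is small at a correlation of 0.2, where neither analysis is likely to detect anything. It is substantial at 0.4-0.5, where about 57-85% power falls to 19-49% (Wald) or 31-63% (LR).

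Dichotomising accounts for most of this. Leaving age and gender out of equation (2) adds to the loss, and makes the test conservative, only if they are related to severity. Neither feature of the plan inflates false positives. The change should be made, because it needs no new data and can be fixed before analysis.

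**What to change.** Make the confirmatory H1B test a linear regression in the 47 patients: CY-BOCS total on v1 and v2 (each the mean of the 10 segments), age, gender and age×gender. Test b1 and b2 each at 1.25%. The normal q-q check planned for Model 1B then suits the model, and covariates are handled as in H1A.

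Keep the moderate/severe logistic model as a secondary analysis for classification accuracy, ROC curve, sensitivity and specificity, and state its numerical cut.

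Cost: more than a change to one equation. The H1B hypothesis in the Statistical Analysis Plan section must be reworded from severity classifications to severity scores, with the abstract to match. The confirmatory result becomes a slope in CY-BOCS points rather than an odds ratio. No further data are needed.

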#### Adjusting for Confounding and Calculating Average Features

We expect age and gender to have an influence on the vocal features and would like to remove these confounding effects from the signals. We will exclude effects from age, gender, and age and gender interactions from the vocal features through a linear regression, as follows.

First, we will find the confounding effects using a linear regression model, which estimates age and gender contributions to vocal features as follows:

where, for the *i*th observations and *j*th vocal feature, *j* = 1, 2. The vocal features adjusted for age and gender are then as follows: 

Finally, we will use the average vocal features over the 10 repetitions for the *k*th youth to obtain 

*_jk_* = Σ*iεyouth_k_ v_ji_* / 10.

#### Adjusting for Multiple Testing

We are interested in the null hypotheses associated with the effect of a diagnosis on the two dimensions in the latent model as well as the effects from the two adjusted latent dimensions on the severity scores. We will adjust our 4 *P* values using the Bonferroni method, and thus test each null hypothesis at a 5%/4=1.25% level of significance resulting in a family-wise error rate for the four tests of 5%.

#### Machine Learning Models for Objective 2

To improve the vocal features for possible use as biomarkers of OCD severity, we shall use the following methodology. First, 2 authors ([name]) will annotate samples for activation and valence on a 5-point Likert scale with 1 indicating low activation and 5 indicating high activation. We shall only provide the annotators with one speech segment at a time in a blinded manner and in random order.

For the planned analyses, we will not use the valence labels, but the activation labels as these labels have shown promise in previous investigations [16]. We will use these labels as in our previous work [16]. The major advantages of labeling speech signals with activation scores include making labels for Danish speech and for children’s speech, and labeling speech of patients and controls. Thus, the labels provide added information as no open source data exist, thus supporting transfer learning wherever feasible.

Subsequently, we shall train the following machine learning models using the following annotations: variational and denoising autoencoders with semisupervised losses based on activation labels and a reconstruction error, plus a logistic regression or logistic regression loss in a neural network to obtain a classification model.

### Model Validation Strategies

We will use a leave-two-youth-out cross-validation, leaving 1 control plus 1 patient out for validation in each fold to tune the hyperparameters in our machine learning models and to choose between a simple logistic regression or a neural network with a logistic regression loss. To validate the results, we will use an independent test set of 10 interviews (5 with the patients and 5 with the controls) to evaluate the performance of these methods. These interviews will be transferred at the time of the independent test.

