**Methods:**

Audio recordings of clinical interviews of 47 children and adolescents with OCD and 17 children and adolescents without a psychiatric diagnosis will be analyzed. Youths were between 8 and 17 years old. We will test the effect of OCD diagnosis on computationally derived scores of vocal activation using ANOVA. To test the effect of OCD severity classifications on the same computationally derived vocal scores, we will perform a logistic regression. Finally, we will attempt to create an improved indicator of OCD severity by refining the model with more relevant labels. Models will be adjusted for age and gender. Model validation strategies are outlined.

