#### Audio Features

From each speaker segment, we will extract the extended Geneva minimalistic acoustic parameter set [23], consisting of functionals of lower-level features. We will use the OpenSmile toolkit to extract these features and the resulting feature vector has a length of 88 [24].

The derived feature vector will be used as input to a neural network autoencoder model to obtain a latent model. The latent model is pretrained on English speech using the Interactive Emotional Dyadic Motion Capture data set and a semisupervised loss as previously described [16]. The latent model is a 2D latent space (*v*1 and *v*2) in a semisupervised denoising autoencoder with a reconstruction loss plus a loss based on the linear association between the activation labels and the latent space (the aim is a high association). Thus, to obtain *v*1 and *v*2, the 88 vocal features are projected into the latent space through the pretrained network. Previous analyses indicate that this latent space represents 2 dimensions of speech activation or intensity [16]. Sad and bored speech is characterized by low activation whereas elated and angry speech is characterized by high activation [25]. Thus, we assume that this latent space represents emotional intensity. We do not have an objective metric to evaluate this quantitatively using the current data and labels. Therefore, we will test this assumption in future work when more data labels are available. 

For the machine learning analyses, we will use the raw speech signals to learn new features.

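### Objective 2 aims at an improved indicator of OCD severity, but the fixed folds, test set and results table suit OCD versus control, and no same-data comparison with the earlier latent model is stated

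*Protocol article*

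**What the plan says.** **Aim.** The Abstract (Methods) says "we will attempt to create an improved indicator of OCD severity by refining the model with more relevant labels". The second objective in the Statistical Analysis Plan section reads "Learn a new latent model, which we will propose as an improved candidate indicator of OCD severity". Machine Learning Models for Objective 2 opens with the same purpose: "To improve the vocal features for possible use as biomarkers of OCD severity, we shall use the following methodology".

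**Outcomes.** For Objective 2 the Statistical Analysis Plan section says "outcomes will include diagnostic status (OCD vs no psychiatric diagnosis) and OCD severity (CY-BOCS severity scores". It then says that the modelling is validated by leave-two-out cross-validation, by prediction accuracies and by an independent test.

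**Validation.** Model Validation Strategies makes this concrete: "leaving 1 control plus 1 patient out for validation in each fold to tune the hyperparameters in our machine learning models". The same folds choose between a plain logistic regression and a network with a logistic loss. The independent test set is 5 patients and 5 controls.

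**Reporting.** Statistical Report Model 2 gives one simulated set of binary metrics (Table 4: accuracy 0.82, sensitivity 0.78, specificity 0.86, area under the curve 0.89), one ROC curve and one confusion matrix. The table does not name its target. OCD is the only class term in the two figure captions.

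**Age and gender.** The Abstract (Methods) states "Models will be adjusted for age and gender", and its Conclusions count this as a major strength. The written procedure, from Statistical Models to Adjusting for Confounding and Calculating Average Features, concerns the two latent features v1 and v2. For Objective 2, Audio Features says "For the machine learning analyses, we will use the raw speech signals to learn new features".

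**The concern.** The Measures section describes OCD severity as established in patients; for controls, the interviews served to rule out diagnoses. Every patient has a CY-BOCS score of at least 16. Separating such patients from controls therefore says nothing about grading patients between 16 and 40. A scheme that pairs one control with one patient, and a test set of 5 and 5, is natural for diagnosis. No severity-specific fold, metric or results table is stated, although severity is what the new model is to indicate.

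The word *improved* also needs a reference. The stated comparisons are between two classifier types and between validation and training data. The pretrained v1 and v2 are not scored on the same held-out youths.

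The risk is a published candidate severity indicator whose tuning, model choice and final test rest on a patient/control contrast, with no benchmark for the improvement. The protocol's value is that it fixes the analysis in advance, so the mismatch should be settled before the data are analysed.

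**Working it through.** **Inputs from the protocol article:** 47 patients and 17 controls (Participants and Setting); one patient and one control per fold, and a test set of 5 and 5 (Model Validation Strategies); Table 4. It is unclear whether the 10 test youths are among the 64, so both counts are shown: 47 and 17, or 42 and 12.

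**1. The plan's own figure.** Accuracy is the weighted mean of sensitivity and specificity.
- Equal classes: (0.78 + 0.86)/2 = 0.82, which matches Table 4.
- 47:17: (47 × 0.78 + 17 × 0.86)/64 = 0.801.
- 42:12: (42 × 0.78 + 12 × 0.86)/54 = 0.798.

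The match fits a 1:1 patient/control score. The table is a simulated placeholder, so this is consistent with a diagnosis target but does not prove one.

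**2. What the folds can show.** Each fold holds one patient, so no fold can set a moderate case against a more severe one. The number of possible pairs is 47 × 17 = 799, or 42 × 12 = 504. The article does not say whether all pairs are used. If each youth is left out at most once, there are 17 (or 12) folds, and 47 − 17 = 30 (or 42 − 12 = 30) patients are never validated.

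**3. Severity information in the test set: 5 patients.** Clopper-Pearson 95% intervals for a correct severity class:

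| Correct | 95% interval |
|---|---|
| 5 of 5 | 48% to 100% |
| 4 of 5 | 28% to 99.5% |
| 3 of 5 | 15% to 95% |

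For 5 of 5 the lower limit is 0.025^(1/5) = 0.478. Guessing at 50% gets all five right with probability 0.5^5 = 3.1%. The severity split is not given. If the share in one class is assumed to lie between 0.3 and 0.7, the chance that all five patients fall in the same class is p^5 + (1 − p)^5, which runs from 6% (p = 0.5) to 17% (p = 0.3 or 0.7).

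**4. What patient-only cross-validation could offer.** At an assumed accuracy near 81%, the binomial 95% interval is about 66% to 91% for 34 of 42, and 67% to 91% for 38 of 47. These are illustrations, and they treat out-of-fold results as independent.

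**5. Benchmark.** Statistical Report Model 1B does give a severity accuracy for the earlier latent model (80%, simulated), but the illustrated ROC curve and accuracy are on training data. An in-sample figure for the old model and a held-out figure for the new one cannot be compared fairly.

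**6. Age and gender.** The Abstract promises adjustment for the models in general. The adjustment equations index j = 1, 2, that is v1 and v2. Machine Learning Models for Objective 2 lists autoencoder losses and a logistic classifier without saying where age or gender enters. The Strengths section itself notes that pitch differs by gender and that pitch and formants fall with age, so a raw-speech model could pick these up.

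**The case against.** The strongest reply is that severity is not forgotten. The Statistical Analysis Plan section names it as an outcome directly before the validation sentence, and every fold leaves out a patient who has a CY-BOCS score. Predictions for left-out patients could be pooled across folds, as in leave-one-out. This stands: a reader might infer that the study can only ever report diagnosis accuracy, and the document does not support that. What remains is that no pooling step and no severity metric is stated, while tuning and model choice are tied to the control-plus-patient folds.

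Second, Table 4 names no target, the figures are not available, and a condensed article may show only one example. This also stands. A diagnosis target is likely but not proven.

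Third, the aim is hedged as an attempt and a candidate, and Model 1B gives a reference for the earlier latent model. The hedging lowers the stakes, but a training-data reference does not supply the missing comparison.

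Fourth, the Abstract promises age and gender adjustment for the models generally, and an article may omit how it enters a network. A reader might infer that Objective 2 is unadjusted. The text shows only an inconsistency between the general promise and the written procedure. Nor does it show that the groups differ in age or gender, since no distribution by group is given. Any figure for how well age alone would separate the groups would rest on an assumed gap and on speech revealing age without error, so it would be an upper bound.

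**Conclusion.** The concern holds in this form: severity is named as an Objective 2 outcome and is its stated purpose, but it is not carried through to the fold design, the test set or the results table. No fold can contrast severity levels, no severity metric is stated, and the final test has 5 patients with severity information, so even a perfect result leaves a lower 95% limit of 48%. Without scoring v1 and v2 on the same held-out youths, improvement cannot be judged. The age and gender passages are a secondary inconsistency to reconcile.

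The fold and test-set conclusions follow directly from the stated design. The count of 30 patients never validated assumes disjoint folds, and the 6% to 17% range assumes the severity split.

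**What to change.** 1. Keep the control-plus-patient folds for diagnosis. For severity, add patient-only cross-validation with the CY-BOCS score as target, keeping all segments of a youth in one fold. Exclude the 5 test patients if they are among the 47, which leaves 42; tuning on all 47 would then use up the independent test. Report out-of-fold error and rank correlation.
2. In the same folds, score three models: age and gender only; age and gender plus the pretrained v1 and v2; age and gender plus the new features. Report paired differences with bootstrap confidence intervals that resample youths. Call the new model improved only if the interval for new versus pretrained features excludes zero in its favour; otherwise describe it as exploratory.
3. State that the 5-plus-5 test set supports diagnosis only and cannot confirm severity performance.
4. Reconcile the Abstract's age and gender statement with Audio Features and Machine Learning Models for Objective 2, and say how age and gender enter the raw-speech models.

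The cost is more model fits on recordings and scores already held or planned, and edits to the Statistical Analysis Plan, Machine Learning Models for Objective 2, Model Validation Strategies and Statistical Report Model 2 sections. The headline results may look less favourable.
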